# Evaluation design of a reactivation care program to prevent functional loss in hospitalised elderly: A cohort study including a randomised controlled trial

**DOI:** 10.1186/1471-2318-11-36

**Published:** 2011-08-03

## Abstract

**Background:**

Elderly persons admitted to the hospital are at risk for hospital related functional loss. This evaluation aims to compare the effects of different levels of (integrated) health intervention care programs on preventing hospital related functional loss among elderly patients by comparing a new intervention program to two usual care programs.

**Methods/Design:**

This study will include an effect, process and cost evaluation using a mixed methods design of quantitative and qualitative methods. Three hospitals in the Netherlands with different levels of integrated geriatric health care will be evaluated using a quasi-experimental study design. Data collection on outcomes will take place through a prospective cohort study, which will incorporate a nested randomised controlled trial to evaluate the effects of a stay at the centre for prevention and reactivation for patients with complex problems. The study population will consist of elderly persons (65 years or older) at risk for functional loss who are admitted to one of the three hospitals. Data is prospectively collected at time of hospital admission (T0), three months (T1), and twelve months (T2) after hospital admission. Patient and informal caregiver outcomes (e.g. health related quality of life, activities of daily living, burden of care, (re-) admission in hospital or nursing homes, mortality) as well as process measures (e.g. the cooperation and collaboration of multidisciplinary teams, patient and informal caregiver satisfaction with care) will be measured. A qualitative analysis will determine the fidelity of intervention implementation as well as provide further context and explanation for quantitative outcomes. Finally, costs will be determined from a societal viewpoint to allow for cost effectiveness calculations.

**Discussion:**

It is anticipated that higher levels of integrated hospital health care for at risk elderly will result in prevention of loss of functioning and loss of quality of life after hospital discharge as well as in lower burden of care and higher quality of life for informal caregivers. Ultimately, the results of this study may contribute to the implementation of a national integrated health care program to prevent hospital related functional loss among elderly patients.

**Trial registration:**

The Netherlands National Trial Register: NTR2317

## Background

Hospital admission is considered a risk (especially for older patients), which increases with age [1]. Among 70-year olds who are admitted in the hospital, 35% show functional loss at time of discharge when compared to the period before hospital admission, and this percentage rises as high as 65% for persons aged 90 years or older [2]. Hospital related functional loss among elderly is often associated with the risk of developing complications due to an illness or its treatment [1]. Nevertheless, functional loss among elderly persons is only partly the result of the patient's diagnosed illness at admission and treatment thereof [2], implicating that a hospital stay by itself leads to functional loss as well. Functional loss may lead to renewed hospital admission, prolonged hospital stay, admission in a nursing home or even early death [3,4]. Furthermore, it will lead to greater dependence, resulting in a higher burden of care for informal caregivers [2,5-7], higher utilization of professional health care and thus higher health care costs [8]. It is therefore important to prevent or reduce functional loss among elderly at an early stage [9].

Risk factors for functional loss are highly prevalent among elderly patients at time of hospital admission [10] and can be categorized into several domains: 1) physical status (e.g. age, functioning prior to admission to hospital, diagnosis, co-morbidities, low Body Mass Index/malnutrition, tendency to fall); 2) mental status (e.g. cognitive problems, delirium, depression, anxiety); 3) socio-economic situation (e.g. financial environment) and social environment (e.g. living arrangements prior to admission) as well as aspects regarding care such as poly pharmacy [2,5,8,11-21]. Even though functional loss is a recurrent problem among hospitalised elderly patients, hospital care is usually primarily focused on treating the medically diagnosed illness, thereby often neglecting reactivation care that may prevent functional loss. A "paralleled focused" treatment on reactivation treatment next to treatment of medical diagnosis may preserve functioning of the elderly patient at risk, thereby possibly maintaining quality of life and independence in activities of daily living in the period after discharge from the hospital, which in turn may lead to a lower burden of care for the informal caregivers of these patients as well as lower health care costs at a societal level. This article describes the study design (e.g. methods, setting, population, strengths, and weaknesses) of an evaluation study of a hospital based reactivation care program that is developed to provide reactivation care parallel with regular medical care. This new intervention program will be further referred to in this article as "the program" and will be compared to two control hospitals offering different levels of usual care.

### Description of the hospital based reactivation care program

The program is developed to prevent and/or reduce hospital related functional loss among at risk elderly by offering an individualized treatment plan that is based on problem-solving principles. It includes interventions that are integrated, multidisciplinary and goal-oriented at physical, social, and psychological domains of functional loss and combines existing treatment methods and routes for reactivating at risk elderly persons into an individual care package.

The program consists of several important elements: First, it aims to identify elderly persons at risk for functional loss at an early stage after hospital admission (= triage within 48 hours of admission). This will make early implementation of interventions possible, which may prevent functional decline and promote a quick return to independent living as well as preserve quality of life [7,22]. Second, the program consists of a combination of integrated interventions offered by a specialized multidisciplinary reactivation team with geriatric expertise. Based on existing literature, this approach is expected to lead to reductions in fall incidence, improved functioning, reduced length of hospital stay, lower (re)admissions to hospital and nursing homes, improved mental well-being of informal caregivers and higher perceived health and life satisfaction among patients as well as better coordination of treatment and follow up between different health care providers and finally, lower mortality [23-34]. Third, the multidisciplinary team uses Goal Attainment Scaling (GAS) to develop and monitor a personalized treatment plan. The GAS method has been successful in maintaining/improving functioning of elderly patients with complex health issues [35,36] and has been standardized for this population [37]. The GAS method consists of several phases: The multidisciplinary team identifies the baseline status of the patient and determines a goal. Then the team will monitor the development per patient and their informal care system by measuring progress regularly, making it possible to adjust interventions and/or goals when necessary. A final GAS measurement will take place to set up a follow up treatment plan before the patient is discharged to the home environment. The fourth element of the program is the possibility for patients with complex problems to be referred by the multidisciplinary team to a stay at a specialized centre for prevention and reactivation (further referred to in this article as "the reactivation centre" or "the centre"). The centre offers a combination of interventions aimed at improving a patient's ability to live as independently as possible in the home environment by providing extra-intensive thematic reactivation treatment alongside regular provisions. It includes specialized nursing home care, paramedical care, specialized mental health care, and treatment and consultations for primary informal caregivers if needed. Patients stay at the reactivation centre for a maximum of three months, after which the multidisciplinary team will develop an individual care-plan for follow up after discharge. Finally, the program will provide support to patients and their informal caregivers by means of a case manager with geriatric expertise who is involved in all aspects of care throughout the period of hospital stay as well as during the follow up period after hospital discharge (irrespective of a patient's destination after discharge whether this is their independent home, the centre for prevention and recovery, a nursing home or any other setting). The case manager is involved in identifying at risk patients in the hospital, coordinating the individual's care plan, coordinating follow up health care for a patient after discharge (e.g. in cooperation with general practitioner, home care or other first line care providers) and aims to support and motivate the patient in treatment adherence. In addition the case manager monitors a patient's risk factors for functional loss throughout all phases of care and may plan extra treatment if necessary as well as improve the care process where possible. Previous programs focused on case management or follow up care have lead to reductions in hospital admissions, nursing home admissions as well as a reduction in length of hospital stay [38,39]. Furthermore, case management may lead to improved access to health care, increased psychosocial support and improved communication with health professionals as valued by patients and their informal caregivers [40].

Even though earlier studies have shown the benefits of specialized multidisciplinary geriatric inpatient reactivation interventions (as well as similar programs for elderly persons living at home), insufficient data is available on programs offering a combination of abovementioned successful elements of care, their cost-effectiveness, and on how to define the patient group that benefits the most from these programs [39,41-45]. To our knowledge, the current evaluation of the new intervention program is the first to offer results on the effects of a combination of several successful elements of care as well as offer clear patient eligibility criteria for such an integrated program.

### Objectives of the evaluation

This evaluation study entails an effect, process and cost evaluation of offered geriatric health care and has four main objectives. First of all, the study aims to determine to what extent the program, in comparison with other usual forms of geriatric care, leads to a retention in functioning and quality of life of at risk elderly, a reduction in the burden of care for the patient's primary informal caregiver, shorter lengths of hospital stay, and a reduction of 'wrong bed' problems as well as (re-) admission to hospitals, nursing homes and mortality. In addition, it will show the extent to which program care including a stay at a reactivation centre, leads to better functioning and quality of life of elderly patients in need of complex care. Secondly, the study aims to determine to what extent the triage instruments used in the program detect increased risk for functional loss and to determine how criteria for triage should be adjusted to optimally link the offered interventions to the needs of the individual elderly at risk. Thirdly, the evaluation will determine to what extent the program, in comparison with other, usual forms of geriatric care in the Netherlands, leads to a better structure and process of care. Finally, the cost-effectiveness of the program (both including and excluding a stay at a reactivation centre) will be determined in comparison with other usual forms of geriatric hospital care in the Netherlands.

## Methods/Design

### Evaluation design

This evaluation study uses a concurrent mixed methods design (a combination of qualitative and quantitative research methods) to evaluate triage criteria, effects, processes and costs of the care provided in the three hospitals. It consists of a quasi-experimental study as well as a nested randomised controlled trial. Within the quasi-experimental study, the data collection of health care costs and outcomes on functional status and quality of life for patient and caregiver as well as other outcome measures such as cognitive functioning, duration of hospital stay and mortality of patients will be measured using a prospective cohort design. The "reactivation centre" component will be evaluated using a randomised controlled trial. Patients eligible for a stay at the reactivation centre will be randomised to program treatment with a stay at the centre or program treatment without a stay at the centre. The effects of a stay in the reactivation centre will be measured at three months after hospital admission and the effects of a centre stay in combination with program aftercare at home will be evaluated at twelve months after hospital admission. In addition, a set of quantitative process indicators will be collected both for program treatment with and without a stay at the centre (e.g. which disciplines were involved in treatment, how soon after admission the treatment started). For an in-depth evaluation of the effects of the program, data is collected on the differences in the healthcare processes between the three hospitals as well as differences in offered follow up care between the three hospitals. Qualitative data will be collected through interviews, observations and document analysis at similar times as the effect evaluation. These qualitative measures will support the comparison of the quality of care processes between the three hospitals.

The study protocol was approved by the medical ethics committee of the Erasmus Medical Centre, Rotterdam, the Netherlands, under protocol number MEC2011-041.

### Setting

Three hospitals with different levels of geriatric care will be compared in this evaluation. The first hospital (Ruwaard van Putten, Spijkenisse) offers care without clinical geriatrics, with hospital replacement care through a care hotel and no follow up in primary care. The second hospital (St. Franciscus Gasthuis, Rotterdam) offers care with coordinated discharge and hospital replacement care (through care hotel "Aafje") and without follow up in primary care. The third hospital (Vlietland + Argos Zorggroep, Nieuwe Waterweg, Noord) is the intervention hospital and offers the new hospital based reactivation care program which includes clinical geriatrics, intensive reactivation care after hospital stay (through a stay at the centre for prevention and reactivation) and with follow up in primary care (through case management). The three hospitals have been chosen as they are similar in patient case mix as well as offer geriatric care in different dosages and with different elements of care.

### Pilot study

A pilot study was conducted in the intervention hospital (Vlietland hospital) to choose the best triage instruments to identify elderly patients eligible for the reactivation program. Furthermore, the pilot results will be used to identify possible practical implementation problems in preparation for the main evaluation study and serve as base for power calculations for the main study. In the pilot study, all patients (65 years or older) who were admitted to the Vlietland hospital between June 2010 and October 2010, were asked to participate. Around 500 patients and 200 informal caregivers were included at baseline (within 48 hours after hospital admission) and of this group around 300 patients and 160 informal caregivers completed questionnaires at the 3-month follow up (see figure 1: Flow chart pilot study). Follow up measurements at twelve months after hospital admission will be finalized in November/December 2011.

**Figure 1 F1:**
[figure not shown]
**Flow chart pilot study**.

### Participants

#### Population

The target population of the study consists of elderly persons (65 years and older) who are at risk for functional loss and are admitted to one of the three hospitals for at least two days. All patients will receive the usual care offered by each of the hospitals. All relevant hospital departments will be included in the study and admission may be elective or acute. Figures 2 and 3 (flowcharts) provide an overview of the flow of patients in the study. Through a first triage step, all patients at risk for functional loss will be identified with the ISAR-HP [46,47]. These at risk patients will be eligible to receive the hospital based reactivation care program and therefore will be asked to participate in the study. In the Vlietland hospital, an additional triage will take place using the short Neuropsychiatric Inventory [48,49] and the Mini Mental State Examination [50] to identify elderly patients eligible for a stay at the reactivation centre. This group will then be randomised to program care including a stay at the centre (n = 200) or program care excluding a stay at the centre (n = 200). The primary informal caregivers of the participating patients will be asked to answer several questions about the patient in a telephone interview as well as fill out mailed paper questionnaires on quality of life, burden of care and other outcomes at time of hospital admission of the patient, three months after hospital admission and twelve months after hospital admission. Furthermore, health care professionals from each participating hospital will be asked to complete a survey on processes of health care.

**Figure 2 F2:**
[figure not shown]
**Flow chart intervention hospital**.

**Figure 3 F3:**
[figure not shown]
**Flow chart control hospitals**.

#### Inclusion criteria

• patients aged 65 years or older

• admitted in one of the participating hospitals and staying >48 hours

• at risk for functional loss (ISAR HP ≥ 1)

Additional criteria for a stay at the centre for prevention and recovery

• ISAR HP ≥ 2 and/or MMSE ≤ 27 and/or NPI ≥ 3

#### Exclusion criteria

• Unable to answer questions or follow instructions (e.g. due to severe cognitive problems (MMSE score <12/delirium/coma) within 48 hours of admission in the hospital

• Not able to understand the Dutch language

• Life expectancy <3 months.

#### Power calculation and effect size

For the prospective cohort we expect to be able to collect a sample size of around 1100 patients in the intervention hospital (900 patients treated with the new intervention program and 200 patients treated with the new intervention program including a stay at the reactivation centre). Samples of minimal 500 to 600 patients will be collected in each of the two control hospitals. These estimations are based on the average number of elderly patients who are admitted to the different hospitals during our inclusion period of one year. According to preliminary pilot results on activities of daily living (Katz-15 ADL score), a population of n = 500 in the control hospitals will lead to around n = 300 persons analyzable at three months, whereas a baseline population of n = 1100 in the intervention hospital will lead to around 733 persons analyzable at three months. Using an effect size of 0.25 this will lead to a power of 95% [46]. Furthermore, to detect a smaller effect size (Cohen's D of 0.2), n = 1100 in the intervention hospital and n = 500 for the control hospitals will lead to a power of 83%. If possible, we will aim for a larger sample size in the control hospitals than the expected n = 500, (preferably 900), which will lead to N = 733 analyzable in the intervention hospital versus n = 600 analyzable in the control hospitals, with an effect size of 0.2 leading to a power of 95%. Abovementioned sample sizes are large enough to allow for reliable analysis per subgroup (e.g. subgroup of specific diagnoses) and sets of risk factors.

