### Data collection

There is no clear consensus on the time period during which effects of interventions on physical functioning and quality of life will be maintained. In some studies effects were present at six to twelve months after the start of the intervention, with the largest effect present around three months [24,26]. Therefore, main data collection of patient and caregiver outcomes takes place at time of hospital admission (T0), three months after hospital admission (T1) and twelve months after hospital admission (T2). Trained research nurses and students will administer questionnaires to patients by means of interviews at T0, T1 and T2. Furthermore, informal caregivers will receive paper questionnaires sent by mail. Patient and caregiver outcome measures will then be compared between the three hospitals. In addition a survey is administered among personnel of the three hospitals at one time during the second half of the inclusion period. Additional triage, outcomes, process, and cost information is collected from patient files and hospital ICT systems at time of discharge, during the intervention and in retrospect. Based on the pilot results we expect around 60% of patients analysable at 3 month follow up. Loss to follow up is minimized by making house calls and interviewing the patients in person [51]. Tables 1, 2, 3, 4 and 5 show a complete overview of outcome variables and data collection instruments for demographics and triage (table 1), effect evaluation (tables 2 and 3), process evaluation (table 4) and cost evaluation (table 5).

**Table 1 T1:** Data collection of patient and informal caregiver: demographics and triage

Evaluation	Variables and+ instruments	Data collection methods	Data collection times			**Notes**:
			**T0**	**T1**	**T2**	

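### The power section mixes two three-month follow-up rates (60% and 67%) where the rest of the protocol gives only 60%; two analysable numbers are about 11% too high, with little effect on power

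*Protocol article*

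**What the plan says.** The section on power and effect size of the protocol article turns baseline numbers into patients analysable at three months and cites preliminary pilot results on the Katz-15 as its basis. For the controls, "a population of n = 500 in the control hospitals will lead to around n = 300 persons analyzable at three months". In the same sentence, for the programme arm, "a baseline population of n = 1100 in the intervention hospital will lead to around 733 persons analyzable at three months". On these numbers, "Using an effect size of 0.25 this will lead to a power of 95" per cent, and at an effect size of 0.2 the power is put at 83%. The section then gives a more hopeful scenario: "we will aim for a larger sample size in the control hospitals than the expected n = 500, (preferably 900"), which yields "N = 733 analyzable in the intervention hospital versus n = 600 analyzable in the control hospitals" and a power of 95% at 0.2.

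Two other sections bear on the follow-up rate. Under Pilot study, about 500 patients were included at baseline in the intervention hospital, and "around 300 patients and 160 informal caregivers completed questionnaires at the 3-month follow up". Under Data collection: "Based on the pilot results we expect around 60% of patients analysable at 3 month follow up". That last statement does not distinguish between hospitals.

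**The concern.** The power section gives one source for its analysable numbers, the pilot, but two follow-up rates come out of it. The control figure at 500 matches the pilot. The intervention figure does not, although the pilot was run in that hospital. The control rate itself also rises from 60% to two thirds when 900 rather than 500 are enrolled, and enrolling more patients is no reason to expect better follow-up.

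The analysable numbers are what the three power figures rest on. The section also relies on its sample sizes when it says that subgroups can be analysed reliably. A reader cannot tell which follow-up rate the study is planned on, and two of the three distinct analysable numbers do not follow from the rate given elsewhere.

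**Working it through.** **Inputs.** From the power section: 1100 → 733 (intervention), 500 → 300 (controls), 900 → 600 (controls, larger scenario); effect sizes 0.25 and 0.2; stated powers 95%, 83% and 95%. From the pilot section: about 500 → 300. From the data-collection section: about 60%. The significance level and sidedness are not stated; two-sided 5% is my assumption.

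**Step 1: implied follow-up rates.**
- Pilot: 300/500 = 60.0%
- Controls, basic scenario: 300/500 = 60.0%
- Intervention hospital: 733/1100 = 66.6%
- Controls, larger scenario: 600/900 = 66.7%

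Two thirds of 1100 is 733.3 and two thirds of 900 is 600, so both higher figures look like a two-thirds rule.

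**Step 2: reproduce the stated powers.** For two groups of n₁ and n₂ and a standardised difference d, power ≈ Φ(d·√(n₁n₂/(n₁+n₂)) − 1.96). The table gives the exact noncentral-t values, which agree with this approximation to within 0.1 percentage point.

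| Analysable | d | d·√(n₁n₂/(n₁+n₂)) | Power | Stated |
|---|---|---|---|---|
| 733 v 300 | 0.25 | 0.25·√212.9 = 3.65 | 95.4% | 95% |
| 733 v 300 | 0.20 | 0.20·√212.9 = 2.92 | 83.0% | 83% |
| 733 v 600 | 0.20 | 0.20·√329.9 = 3.63 | 95.3% | 95% |

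All three are reproduced. A one-sided 5% test would give 97.7%, 89.8% and 97.7%, which does not fit. Baseline numbers (1100 v 500 at d = 0.2) would give 96.0%, so the stated 83% does rest on 733 v 300.

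**Step 3: apply 60% throughout.**
- 0.60 × 1100 = 660; 733 exceeds it by 73, and 733/660 = 1.11.
- 0.60 × 900 = 540; 600 exceeds it by 60, and 600/540 = 1.11.
- 0.60 × 500 = 300, unchanged.

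| Analysable | d | d·√(n₁n₂/(n₁+n₂)) | Power at 60% | Stated |
|---|---|---|---|---|
| 660 v 300 | 0.25 | 0.25·√206.3 = 3.59 | 94.8% | 95% |
| 660 v 300 | 0.20 | 0.20·√206.3 = 2.87 | 81.8% | 83% |
| 660 v 540 | 0.20 | 0.20·√297.0 = 3.45 | 93.1% | 95% |

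The first power is unchanged after rounding. The second is about one point lower and the third about two.

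**Step 4: why so little changes.** In the first two scenarios the smaller group, the 300 controls, dominates the power, and that figure already uses 60%. Cutting the larger group from 733 to 660 lowers n₁n₂/(n₁+n₂) only from 212.9 to 206.3.

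**The case against.** The best defence is that this hardly matters. Every scenario stays above 80%, and the only fall of about two points is in a scenario that the protocol presents as a hope. The plan's own recruitment range has a larger effect: the protocol expects at least 500 to 600 patients in each control hospital, and 600 at 60% gives 360 analysable. Then 660 v 360 at d = 0.2 has 86.2% power, so the stated 83% lies inside the range of 81.8% to 86.2% that the plan supports even at 60%. Recruitment was set by admissions over a year, not by a power target, so no recruitment number depends on the higher rate. All of this stands, and it keeps the point small.

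It does not remove the inconsistency. The word 'around' does not cover an 11% excess. The planned house calls do not explain it, because the 60% appears in the same paragraph as the house calls, which are not confined to one hospital. Nor can the choice of the Katz-15 explain it, since both rates in the sentence are attributed to the same pilot results on that scale. This is also not a detail that a condensed article leaves out: the conflicting figures are all printed.

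Three stronger readings are tempting but not supported:
- **All the power figures use 67%.** They do not; the 300 controls in the first two scenarios rest on 60%.
- **The study expects, and is biased by, unequal loss between hospitals.** The larger scenario uses 67% on both sides, which speaks against a deliberate assumption of unequal loss, and a planning rate does not itself create bias.
- **The control figures are for one hospital.** The expected recruitment is given per control hospital, but the power sentences speak of the control hospitals in the plural. If 500 is per hospital and the two are pooled, 60% gives 600 analysable controls, and 660 v 600 at d = 0.2 has 94.3% power. The text does not settle which is meant.

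**Conclusion.** The point holds as an internal inconsistency in the stated sample sizes. The power section uses 60% in one place and 67% in two others without explanation, while the pilot and data-collection sections support only about 60%. On that rate, 733 and 600 are each about 11% too high.

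The powers of 94.8%, 81.8% and 93.1% rest on three assumptions: a two-sided 5% test, a simple comparison of two means, and the group sizes as the protocol pairs them. The study should not be read as underpowered on this account.

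**What to change.** Apply the 60% rate throughout the power section, or give the reason for 67% and bring the data-collection section into line with it. At 60%, restate the analysable numbers as 660 in the intervention hospital and 300 (or 540 in the larger scenario) in the controls. Restate the powers as 95% at 0.25, 82% at 0.2 and, for the larger scenario, 93% at 0.2. State the significance level and sidedness. Say whether 500, 300, 900 and 600 refer to each control hospital or to both combined, and recompute if they are combined.

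The cost is a few sentences and slightly less favourable figures. Recruitment and design stay as they are.

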#### Effect evaluation and process evaluation

##### Effects and process evaluation of the hospital based reactivation care program

Corrections will take place by means of 'analysis of covariance' for baseline differences in determinants between the locations that could explain differences in functioning or quality of life. Multiple regression analysis will be administered for various outcome variables such as linear regression for continuous outcomes; logistic regression for dichotomous outcomes; proportional odds regression for orderly outcomes and Cox proportional hazards regression for events that occur over time (such as death). Analysis of outcomes at three and twelve months will take into account dependency of these outcomes within persons. The degree of exposure to integrated, multidisciplinary care within the intervention location (process evaluation) will also be correlated with effect measurements in order to see whether greater exposure leads to greater effects. Regression analysis will trace sub-group effects and an interaction term will be included in the model, between type of hospital and sub group (e.g. elderly at high risk for functional loss in comparison to elderly at relatively lower risk for functional loss).

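### The assurance of reliable analysis per subgroup is contradicted by the plan's own power figures for diagnosis-sized subgroups and for the hospital-by-subgroup interaction

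*Protocol article*

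**What the plan says.** The section *Power calculation and effect size* gives expected numbers at three months: "a population of n = 500 in the control hospitals will lead to around n = 300 persons analyzable at three months", and "a baseline population of n = 1100 in the intervention hospital will lead to around 733 persons analyzable at three months". For these numbers it states: "Using an effect size of 0.25 this will lead to a power of 95" per cent. For an effect of 0.2 it gives: "n = 500 for the control hospitals will lead to a power of 83" per cent. It then describes a larger control sample, to be sought if possible, which gives 733 versus 600 analysable and 95% power at 0.2. All three figures concern the whole-cohort comparison between hospitals.

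The paragraph closes with the assurance: "Abovementioned sample sizes are large enough to allow for reliable analysis per subgroup (e.g. subgroup of specific diagnoses) and sets of risk factors". No subgroup size, subgroup effect, subgroup power or interaction power accompanies it.

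The analysis section for the hospital programme shows how subgroups will be examined: "Regression analysis will trace sub-group effects and an interaction term will be included in the model". The term is between type of hospital and subgroup, with higher- versus lower-risk patients as the example.

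**The concern.** This is a positive statement about the design, not a detail left to a later analysis plan. The whole cohort has 83% power at 0.2 with 300 controls, so little is left to spend on dividing it. A single diagnosis will hold only a fraction of the patients, because all relevant departments and both elective and acute admissions are included. An interaction contrast is less precise again than the overall contrast.

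If the sentence stands, diagnosis-specific findings could later be presented as prospectively supported. In fact they would come from tests that usually miss effects of the planned size and, when they do reach significance, tend to overstate them.

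**Working it through.** **Inputs from the article.** Analysable at three months: 733 intervention, and 300 or 600 control. Planning effects: d = 0.20 and 0.25 (SD = 1).

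**Assumptions.** Two-sided 5% level, independent patients, no covariate adjustment, and a subgroup taking the same share f of each group. The article gives no shares; 10% to 25% is taken as diagnosis-sized, and 50% is added for comparison.

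**Step 1: reproduce the stated powers.** SE = sqrt(1/n1 + 1/n2); power = Φ(d/SE − 1.96).

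- 733 v 300: SE = sqrt(0.001364 + 0.003333) = 0.0685. At d = 0.25, Φ(3.648 − 1.96) = 95.4% (stated 95%). At d = 0.20, Φ(2.918 − 1.96) = 83.1% (stated 83%).
- 733 v 600: SE = sqrt(0.001364 + 0.001667) = 0.0551. At d = 0.20, Φ(3.633 − 1.96) = 95.3% (stated 95%).

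A one-sided 5% level reproduces none of the three, so two-sided 5% is the natural reading. A noncentral-t calculation gives 95.4%, 83.0% and 95.3%.

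**Step 2: power within a subgroup.** SE becomes SE/sqrt(f). Power at d = 0.20 / 0.25:

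| Share f | 733 v 300 base | 733 v 600 base |
|---|---|---|
| 10% | 15% / 21% | 21% / 30% |
| 20% | 26% / 37% | 37% / 53% |
| 25% | 31% / 45% | 44% / 62% |
| 50% | 54% / 73% | 73% / 90% |

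**Step 3: share needed for 80% power.** f = (2.80 × SE/d)², with 2.80 = 1.96 + 0.84.

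- 300 controls: 92% of the cohort at d = 0.20, 59% at d = 0.25.
- 600 controls: 59% at d = 0.20, 38% at d = 0.25.

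**Step 4: the interaction.** SE(interaction) = SE × sqrt(1/f + 1/(1 − f)). The multiplier is smallest at f = 0.5, where it equals 2. Power when the two subgroup effects differ by 0.20 / 0.25 SD:

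| Split | 733 v 300 | 733 v 600 |
|---|---|---|
| 10/90 | 14% / 19% | 19% / 28% |
| 25/75 | 24% / 35% | 35% / 50% |
| 50/50 | 31% / 45% | 44% / 62% |

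The even split is the most favourable, so no split reaches 80% at either size of difference in either scenario. The interaction detectable with 80% power at an even split is 2.80 × 2 × 0.0685 = 0.38 SD with 300 controls and 2.80 × 2 × 0.0551 = 0.31 SD with 600. Both exceed the main effects for which the study was sized.

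**The case against.** **Large subgroups can be adequate.** A reader might infer that the assurance is false for every subgroup. The figures do not support that. A half-cohort subgroup has 73% power at d = 0.25 with 300 controls, and 73% / 90% at d = 0.20 / 0.25 with 600. Subgroups above the shares in step 3 reach 80%. This stands, and it limits the point to smaller subgroups and to the interaction.

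**The control group may be larger than 300.** The article plans at least 500 to 600 patients in each of two control hospitals. Pooled, at 60% analysable, that is 600 to 720. The 600 scenario therefore deserves equal weight and is shown throughout. Even 720 does not change the conclusion: SE = sqrt(1/733 + 1/720) = 0.0525. Doubled to 0.105, for a 25% subgroup or an even-split interaction, this gives Φ(0.25/0.105 − 1.96) = 66% at 0.25.

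**Key quantities are the reviewer's.** The article does not define reliable as 80% power and gives no subgroup shares, and the interaction is set equal to the planning effects for illustration. That is fair. Even so, 15% to 45% would not ordinarily be called reliable, and no single diagnosis is likely to hold the shares that step 3 requires.

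**Covariate adjustment is planned and raises power.** It does, but not enough. With an assumed baseline correlation of 0.5, a 20% subgroup (60 v 147) reaches 33% / 47%.

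**The centre trial.** A reader might extend the point to the nested randomised comparison of 200 versus 200. The sentence closes a paragraph about the prospective cohort, and the article gives neither a power nor a planning effect for that trial. The 0.20 and 0.25 are between-hospital effects. Nothing in the article says that a null centre result would be read as no effect. The centre trial is not part of this point.

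**Sets of risk factors.** The same sentence covers these, plausibly meaning the predictive models in the triage analysis. Power for a treatment contrast does not test that part.

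**Conclusion.** The concern holds in this limited form. The stated power calculations are arithmetically sound; what fails is the assurance drawn from them. For diagnosis-sized subgroups (assumed 10% to 25% of each group), power at d = 0.20 to 0.25 is about 15% to 45% with 300 analysable controls and 21% to 62% with 600. For the most favourable interaction split it is 31% to 45% and 44% to 62%. The assurance is tenable only for large subgroups under the favourable assumptions.

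The conclusion rests on the inferred two-sided 5% level, independent patients, the assumed shares, and interactions no larger than the planning effects. It does not say that every subgroup is undersized, and it makes no claim about the risk-factor models.

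**What to change.** In *Power calculation and effect size*, withdraw the assurance as it applies to subgroups and specific diagnoses. Replace it with a statement that:

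- the sample sizes are justified for the overall between-hospital contrast;
- with patients treated as independent and a two-sided 5% level, an even-split hospital-by-subgroup interaction must be about 0.38 SD (300 analysable controls) or 0.31 SD (600) for 80% power, and larger for uneven splits;
- diagnosis-specific results are exploratory and will be reported as estimates with confidence intervals.

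If the remark on sets of risk factors is kept, it should stand apart with its own justification. The example of higher- versus lower-risk patients can stay as it is; making it the only interaction test would be a design decision, and this correction does not need it.

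The change is to wording only: no sample size, data collection or model changes. The cost is a less favourable stated claim.
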